### Randomisation and blinding

Once consent has been obtained from participants, their information will be entered onto a web-based randomisation system (set up by University of Nottingham Clinical Trials Unit; CTU). The arm to which a participant is assigned will be determined by a computer generated pseudo-random code using random permuted blocks of varying size, created by the Nottingham CTU in accordance with their standard operating procedure and held on a secure server. Participants will be allocated with equal probability to each arm (QbO and QbB) with stratification by site. All participants will undergo the same research measures, including the QbTest. It is the time at which the report is made available to the clinician and patient that is randomised (immediately vs 6 months later). Outcome assessors for all measures will be blind to which arm the participant is in. There are no anticipated events.

In which participant unblinding would be necessary. There is an allocated unblinded research team member ([name]) to provide control checks where required.

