## Methods and analysis

### Trial design

This study is a parallel group single-blind multicentre RCT, exploring feasibility and acceptability, using quantitative and qualitative and health economic evaluations. The study consists of two arms:
QbOpen (QbO): In this arm of the trial participants will complete the QbTest and clinicians, participants and their families will have immediate access to a QbTest report.QbBlind (QbB): In this arm of the trial participants will complete the QbTest but the QbTest report will be withheld from the clinician, participant and patient's family until the last outcome measure is completed at 6 months. All participants will receive the same intervention. Specifically, this will be assessment as usual plus a QbTest as part of the diagnostic assessment.

The patients usual care team will be responsible for conducting the QbTest in clinic appointments. The QbTest will be only be conducted by trained QbTest clinicians.

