### Measures

Blinded members of the research team ([name], [name], [name],) will be fully trained in all trial assessments and responsible for monitoring the distribution, completion and collection of all outcome measures.

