#### Primary outcome

The primary outcome is the number of consultations until a confirmed clinical diagnosis is reached, as recorded on a short pro-forma. The pro-forma will be completed by clinicians after each consultation with the young person and/or family and documents information about appointment duration, diagnosis and medication/treatment. The pro-forma can be provided by contacting the corresponding author.

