#### Other measures

Development and Well-being Assessment (DAWBA^29^): The DAWBA is a semistructured, investigator-based diagnostic interview for child mental health problems, including ADHD, which includes the (Strengths and Difficulties Questionnaire; SDQ^30^) as an initial screen. The parent and teacher DAWBA will be completed to compare the accuracy of clinic diagnosis (in QbO and QbB arms of the trial) to that of an independent clinical consensus diagnosis made using the DAWBA. Two experienced clinicians, blind to allocation, will review the DAWBA and arrive at a clinical consensus diagnosis.QbTest scores: Q-scores for attention, impulsivity and activity will be compared with DAWBA ADHD diagnosis to obtain the best predictive model based on QbTest scores that discriminates between ADHD ‘positive’ and ADHD ‘negative’ gold standard DAWBA diagnosis.Side-effects scale:^31^ Side-effects scale will be completed as a control check in medicated participants to ensure greater speed to diagnosis/medication normalisation is not off-set by greater side effects.SNAP-IV:^32^ The proportion of patients achieving symptom normalisation assessed via the SNAP-IV. If the young person receives a QbTest on medication (Qb2), the timing on the 3-month SNAP-IV will be moved to coincide with Qb2 to provide a direct comparison of subjective (SNAP-IV) and objective (QbTest) measures. The SNAP-IV is a rating scale designed to assess ADHD symptoms.SDQ:^30^ The SDQ is a brief behavioural screening questionnaire which can be used as part of a clinical assessment.C-GAS (Children's Global Assessment Scale^33^): Clinician opinion of patient outcome will be assessed via the C-GAS. The C-GAS is a 0–100 scale which that integrates psychological, social and academic functioning in children.EQ-5D-Y (EuroQol Five Dimensions Heath Questionnaire-Youth^34^): Child health-related quality of life will be assessed using the EQ-5D-Y.A resource collection profile tool will be used. It will encompass elements of a CSRI (Client Service Receipt Inventory^35^) often used in mental health studies but will be a specifically designed economic collection pro-forma for the purpose of this study. It will collect demographic details as well as information on all the services used by the child and family borne costs to be estimated. Indirect costs such as time lost from work incurred by the child's parents or carers will further be recorded. This measure will enable a societal wide perspective for a cost-effectiveness analysis of the QbTest. The DAWBA^29^ QbTest^22^ SDQ^30^ Side-effects scale,^31^ SNAP-IV^32^ C-GAS^33^ EQ-5D-Y^34^ and CSRI^35^ all have established reliability, validity and history of use in clinical and research settings.

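### The article says outcome assessors are blind for all measures, but the primary outcome and the other clinician pro-forma outcomes are decided by clinicians who know the arm

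*Protocol article*

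**What the plan says.** The Randomisation and blinding section makes an unqualified claim: "Outcome assessors for all measures will be blind to which arm the participant is in". Trial design labels the study as follows: "This study is a parallel group single-blind multicentre RCT". It then describes the arms. In QbOpen, "participants will complete the QbTest and clinicians, participants and their families will have immediate access to a QbTest report". In QbBlind, "the QbTest report will be withheld from the clinician, participant and patient's family until the last outcome measure is completed at 6 months".

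On who produces the data, the Primary outcome section says: "The pro-forma will be completed by clinicians after each consultation with the young person and/or family". The primary outcome, the number of consultations to a confirmed clinical diagnosis, is read from that form. Secondary outcomes takes from it the days and minutes to diagnosis, the clinician's confidence rating, and a re-rating of diagnosis and confidence at 6 months. Other measures says: "Clinician opinion of patient outcome will be assessed via the C-GAS". The same section has two experienced clinicians, unaware of allocation, reach the DAWBA consensus diagnosis. The Measures section describes blinded research staff who are trained in the trial's assessments and are "responsible for monitoring the distribution, completion and collection of all outcome measures".

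**The concern.** A reader of the blinding sentence would take the primary outcome to be assessor-blind. It is a count that ends when a clinician judges the diagnosis confirmed, and that clinician either holds the report or knows it has been withheld. Confidence and the 6-month re-rating of the clinician's own diagnosis are judgements by the same informed group.

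If the sentence stands, the trial will be credited with protection against assessment bias on outcomes that lack it. A shorter path to diagnosis in QbOpen could come from the report's content, or from greater readiness to decide because a report is to hand. The article should not suggest that blinding rules out the second explanation.

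**Working it through.** The article gives no figure on this point, so the check sets its statements side by side.

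**Step 1: who knows the arm.** Randomisation and blinding says that what is randomised is when the report reaches clinician and patient. Trial design gives the report to clinician, participant and family at once in QbOpen and withholds it from all three in QbBlind. Receiving or not receiving a report therefore reveals the arm. The report is withheld until the last 6-month measure is complete, so this also applies at the 6-month re-rating.

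**Step 2: who assesses each outcome.**

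| Outcome | Assessor according to the article | Assessor knows the arm? |
|---|---|---|
| Consultations to confirmed diagnosis (primary) | Clinician, on the pro-forma | Yes |
| Days to diagnosis | Same decision, same form | Yes |
| Minutes of visits to diagnosis | Same decision, same form | Yes |
| Diagnostic confidence | Clinician | Yes |
| Stability (6-month re-rating) | Clinician | Yes |
| C-GAS | A clinician; not said to be the treating one, and no blinded rater described | Not settled |
| SNAP-IV, SDQ, side-effects scale | Informants are in Table 1, whose body is not shown; its legend lists clinician, parent/carer and teacher | Yes for any parent-completed form; not stated for teachers |
| DAWBA consensus diagnosis | Two experienced clinicians | Stated to be blind |

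**Step 3: can the blinded research staff supply the missing blinding?** They are trained in the assessments and oversee the handling of forms. Nothing says that they decide when a diagnosis is confirmed, or rate confidence or stability. Those tasks are assigned to clinicians by name.

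**Step 4: result.** All five pro-forma outcomes, including the primary, contradict the claim about all measures. One assessment, the DAWBA consensus, is expressly blind. The remaining scales cannot be classified from the visible text.

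**Size.** The planned difference is 2.94 − 2.18 = 0.76 visits (Sample size and justification). The documents give nothing from which to estimate what part of an observed difference might come from expectation, so no figure is put on it. The sample size calculation is not affected.

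**The case against.** The strongest reply is that clinician access to the report is the intervention. The strengths and limitations box says that the trial studies the effect of an objective technology on clinical decision making. On that view, a clinician who decides sooner because a report is available is largely the effect of interest. The design is also disclosed: the article says single-blind and sets out who sees the report and when. All of this stands, and it is why the point concerns the statement rather than the design. It does not make the claim about all measures true.

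A second reply is that assessors means the blinded research team. The article does not define the term, so that reading is possible. It still leaves the primary outcome in the hands of an informed clinician.

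A third reply is that the article already pairs speed with accuracy. The Introduction's closing aim is faster diagnosis without loss of accuracy, and the Data analysis plan compares accuracy between arms. That is correct, and it means that the interpretation rule proposed below needs no new data.

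A reader might go further and infer that the trial has no protection against assessment bias, or that the blinded staff merely move forms. The documents do not support either. The DAWBA consensus raters are stated to be blind, and the research staff are described as trained in the assessments. Nor can it be asserted that the treating clinician rates the C-GAS or that parents rate the SNAP-IV. The first is not stated, and the second depends on a table body that is not shown.

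**Conclusion.** The claim of blind assessment for all measures is contradicted by the article's own design for the primary outcome and the four other pro-forma outcomes. This rests on explicit text: report timing is randomised, clinicians see or do not see the report, and clinicians decide and record these outcomes. The only inference is that someone who does or does not receive a report knows the arm.

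For the C-GAS the finding is narrower: no blinded rater is described. For symptom scales it is conditional: any form completed by a parent comes from someone who knows the arm. The article does not say that teachers are told the arm, and it does not say whether the analyst is blind.

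The sentence should be corrected because it bears on how the primary result will be judged. Nothing here requires blinded clinicians, a different sample size or a different analysis.

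**What to change.** 1. Replace the sentence in Randomisation and blinding. State that clinicians and families are not blind to arm, and that blinding applies to the DAWBA consensus raters and to the research staff handling the measures. Add the analyst only if the sponsor confirms it.
2. Mark each outcome as blinded or unblinded, for example by a column in Table 1. State who rates the C-GAS and whether that person knows the arm.
3. Add the unblinded primary outcome to Study limitations, which at present discusses only variation in usual assessment between sites.
4. State that a shorter path to diagnosis will be interpreted together with the planned between-arm comparison of accuracy against the blinded DAWBA consensus, in line with the aim in the Introduction.
5. Where Table 1 confirms that teacher versions of a scale are collected, use them as a check on parent and clinician ratings; otherwise do not rely on them.

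The cost is wording and an interpretation rule, with no extra data or staff. The downside is a less favourable risk-of-bias statement for the primary outcome.

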### Data analysis plan

The analysis will be conducted on an intention-to-treat (ITT) basis. Exploratory analysis will be conducted first for outcome and patient background variables; descriptive statistics of each variable will be presented separately for each group at each follow-up point, with means and SD for normally distributed variables, medians (IQR) for skewed variables and frequency (percentage) for categorical variables. Missing values will be checked and reported. Multiple imputation will be used to hand missing values, based on a multilevel modelling approach.

To compare the number of visits needed to achieve an ADHD diagnosis (either confirmed or excluded) between groups, Poisson regression with binary group status as the explanatory variable will be implemented. To compare clinician's confidence in their diagnostic decisions, multilevel modelling with patient as a level 2 unit will be used to take into account the non-independence within patient data due to repeated measures.^41^

κ Statistics will be used to reflect the stability of diagnosis between first confirmed diagnosis and diagnosis rerated at 6-month follow-up time. κ Statistics will be reported for each group and the stability of diagnosis will be compared between arms using logistic regression. The same analysis approach will be implemented to explore the stability of diagnosis confidence between time of first confirmed diagnosis and 6-month follow-up. To assess the diagnosis accuracy, the sensitivity, specificity, likelihood ratio (LR) ve+, LR ve−, positive predictive value (PPV) and negative predictive value (NPV) will be reported for each group and the test performance will be compared between QbO and QbB arms.^42^
^43^ Receiver operating characteristic curve analyses will be used to obtain the best predictive model based on QbTest scores that discriminates between ADHD ‘positive’ and ADHD ‘negative’ gold standard DAWBA diagnoses.

For treatment related outcomes (phase 2) outcome measures such as SNAP-IV, side effects scale, SDQ and C-GAS scores, multilevel modelling with patient as a level 2 unit will be again applied to quantify the difference between QbO and QbB arms.

For time to event variables such as time to diagnosis (in days), survival analysis using log-rank test will be performed for group comparison and Kaplan-Meier survival curves will be displayed for each group. Logistic regression will be used to compare the proportion of normalisation between two groups at 6-month follow-up time. For all regression modelling to explore the difference between arms, group status will be included as explanatory variables. Data transformation would be needed for skewed outcome variables.

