**Figure 1 BMJOPEN2014006838F1:**
[figure not shown]
Study flow chart. ADHD, attention deficit/hyperactivity disorder; CAMHS, Child and Adolescent Mental Health Services.

Phase 1, Assessment: The first phase investigates the use of QbTest as a tool to aid diagnosis. Participants will undergo ADHD ‘assessment as usual’, which varies between clinics, clinicians and cases, but will typically involve an interview with the parent/young person and collection of questionnaires from the parent/young person and teacher. While attending the clinic, the participant will be asked to complete the QbTest at some point during the diagnostic process. Participants will also be asked to complete baseline outcome measures (see measures section).

Phase 2, Treatment: Patients who receive a clinic diagnosis of ADHD and are allocated by clinicians to receive ADHD medication initiated within 3 months of their baseline assessment will be asked to complete a second QbTest (Qb2) 4–8 weeks after medication initiation. This timeframe was chosen to ensure that all participants can complete their second QbTest before the 6-month follow-up.

All participants will stay in the trial for 6 months and will be asked to complete outcome measures at 3 and 6-month follow-up, regardless of their diagnosis or whether they receive medication. With the aim of promoting participant retention and completion of follow-up measures, participants will be compensated for their time with a £15 high-street voucher if they remain in the trial until 6 months.

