
#### Feasibility and acceptability

QbTest opinion questionnaire and interview: Clinician and patient opinion of the QbTest will be assessed via a questionnaire, developed by [name] and currently used to assess QbTest opinion in on-going studies at the Queens Medical Centre, Nottingham. This will provide information on the acceptability of QbTest in routine NHS settings. A subsample (n=20) of families and clinicians will be invited to participate in qualitative interviews to further explore acceptability and feasibility of the QbTest. The subsample will be chosen at random from each participating site, using a random number generator.

Table 1 displays a summary of measures, the informant and the time point of completion. All measures will have a 1-month window for completion, with the exception of the clinic pro-forma which must be completed during or just after the clinic appointment and the QbTest which must form part of the diagnostic or medication assessment. The collected outcome measures for participants who drop out the trial before 6 months will be included in analysis, no further outcome measures will be collected from these participants after they terminate their participation.

**Table 1 BMJOPEN2014006838TB1:** Synoptic table of study measures

[figure not shown]

*If ADHD diagnosis record and medicated within 3 months of baseline assessment (in place of corresponding 3 month assessment in grey).

†Completed at every appointment.

C, clinician completed; P, parent/carer completed; T, teacher completed.

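### The primary count of consultations to diagnosis is right-censored at 6 months or withdrawal, but the planned Poisson regression has no way to represent a censored count

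*Protocol article*

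**What the plan says.** The Primary outcome section defines the endpoint: "The primary outcome is the number of consultations until a confirmed clinical diagnosis is reached, as recorded on a short pro-forma". The Data analysis plan makes clear that ruling ADHD out also counts as reaching the endpoint, since it compares "the number of visits needed to achieve an ADHD diagnosis (either confirmed or excluded) between groups". For that comparison, "Poisson regression with binary group status as the explanatory variable will be implemented".

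Follow-up is limited. Under Trial phases, "All participants will stay in the trial for 6 months". For those who leave early, the data already collected are analysed, but "no further outcome measures will be collected from these participants after they terminate their participation" (Feasibility and acceptability).

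Two general rules in the Data analysis plan could bear on participants without a diagnosis: "The analysis will be conducted on an intention-to-treat (ITT) basis", and "Multiple imputation will be used to hand missing values, based on a multilevel modelling approach". Neither mentions them. The same section treats the same event differently on the day scale: "For time to event variables such as time to diagnosis (in days), survival analysis using log-rank test will be performed", with Kaplan-Meier curves by arm.

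**The concern.** A count of consultations until a decision is complete only if the decision falls inside the observation window. For a participant undecided at 6 months or at withdrawal, the data say only that the count is larger than the visits attended. That is right-censoring, and a Poisson regression on arm has no term for it.

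The stated model therefore leaves three ways to enter such a participant: leave them out, impute the count as if they resembled diagnosed participants, or record visits so far as the final count. All three understate the longest counts. If QbOpen works as intended, more of those counts lie in QbBlind, so the arms are distorted unequally.

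At stake is the primary conclusion. The sample size section treats any difference smaller than 2.94 − 2.18 = 0.76 visits as of doubtful value. Moderate attenuation could therefore make a worthwhile effect look unimportant or non-significant. The choice among the three routes is also left open, and if made after unblinding it could be influenced by the results.

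**Working it through.** **1. The plan's own figure.** Inputs from Sample size and justification: means 2.94 and 2.18, two-sided 5%, 80% power, Poisson counts, 20% attrition. With a Wald test of the log rate ratio:

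n per arm = (z₀.₉₇₅ + z₀.₈₀)² × (1/2.94 + 1/2.18) / [ln(2.94/2.18)]²
= 7.849 × 0.7988 / 0.08945 ≈ 70.1, so 71.

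71/0.8 = 88.75, so 89 per arm and 178 in total, as stated. At 90% power the same formula gives 93.84 per arm and a total of 234.6 (236 if rounded up at each step); a square-root version gives 234. The arithmetic is sound. It assumes that every count is complete: the 20% inflation replaces lost numbers but does not correct for censored counts.

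**2. Effect of the 6-month limit.** The documents give neither visit spacing nor the proportion undiagnosed, so these are assumptions. First visit on day 0, window 182 days, gaps between visits gamma-distributed (shape 4) with the same mean in both arms and unrelated to the number of visits needed. Counts are Poisson with the audit means (true ratio 2.18/2.94 = 0.74), with 71 analysed per arm and 2,000 simulated trials per row. Withdrawal is not simulated separately. Tests use model-based Poisson errors.

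| Mean gap (days) | Undiagnosed QbBlind/QbOpen | Dropped: ratio, power | Visits so far: ratio, power | Log-rank on visit number: power |
|---|---|---|---|---|
| 30 | 3% / 1% | 0.76, 71% | 0.75, 78% | 79% |
| 45 | 13% / 6% | 0.79, 51% | 0.77, 68% | 78% |
| 60 | 25% / 13% | 0.82, 30% | 0.80, 50% | 77% |

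With complete counts the Poisson test has 80%–82% power. Imputing from diagnosed participants of the same arm gives about the same ratio as dropping. Even applied to the full control mean, a ratio of 0.82 would read as 2.94 × (1 − 0.82) = 0.53 visits, below the agreed 0.76.

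**3. Direction.** With no true effect and equal spacing (mean 2.94 in both arms, 45-day gaps, 13% undiagnosed in each), all routes give a ratio of 1.00. With counts of 1 + Poisson, 45-day gaps in QbBlind and gaps 1.5 to 2 times longer in QbOpen, the ratio is about 0.73 to 0.67, further from 1 than the true 0.74.

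**4. Other count shapes.** With geometric (overdispersed) counts and equal gaps of 30 to 60 days, dropping gives 0.82–0.90 and visits so far 0.78–0.85. Log-rank power is then 61%–55%, so the 77%–79% above is specific to Poisson counts.

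**5. How much of the power loss is due to the standard error.** Truncated counts vary less than a Poisson variable, so model-based errors are too wide. Repeating step 2 with the empirical variance (3,000 trials per row; standard error of the log ratio from s²/(n·mean²) summed over arms) gives 74%, 62% and 46% power if dropped, and 79%, 77% and 70% with visits so far. The ratios do not change. Part of the power loss is therefore recoverable with robust errors; the bias in the ratio is not.

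**The case against.** A reader might infer that the plan drops undiagnosed participants. It does not say so. The intention-to-treat statement and the rule that dropouts' collected data are kept point the other way, and nothing labels an undiagnosed child's recorded visits as missing. What stands is that no stated rule covers them and none of the available routes suits the model.

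A reader might also infer that the bias must be toward the null. Step 3 shows that this needs a true effect and similar spacing in the two arms.

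A third tempting reading is that power collapses almost entirely. With counts of 1 + Poisson and a hard limit of 3 visits in 6 months, dropping the undiagnosed does give about 4% power. But the limit and the count shape are not in the documents, and much of the fall reflects underdispersed counts tested with model-based errors: 4.6% becomes 53% with empirical variance. That figure should not be used as the cost of censoring.

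It is fair that coding detail belongs in an analysis plan that is not shown, and that the log-rank analysis of days is a censoring-aware check on a closely related question. But the article fixes the primary model itself, and a secondary analysis in days does not repair a primary estimate in visits. Because excluding ADHD counts as a decision, only unresolved cases and withdrawals are affected, so the problem may be small: at 3% and 1% undiagnosed the ratio shifts only to 0.75–0.76.

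Finally, moving to a hazard ratio leaves the scale on which the trial was sized. That is a real cost and is addressed in the fix.

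**Conclusion.** The concern holds in this form: the primary outcome is right-censored for participants undiagnosed at 6 months or at withdrawal, the stated Poisson regression cannot represent this, and generic multiple imputation does not solve it. The article already uses survival methods for the same event in days.

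The size is conditional. With Poisson counts, equal mean gaps of 30 to 60 days and a true ratio of 0.74, the estimate moves to 0.76–0.82 if undiagnosed participants are dropped and 0.75–0.80 if visits so far are used. Power with model-based errors falls from about 80% to 71%–30% and 78%–50% respectively. These ranges depend on an undiagnosed proportion that the documents do not give. Bias toward the null is the likely direction if QbOpen works and spacing is similar, but it is not guaranteed. The sample size arithmetic itself is not in error.

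**What to change.** Before unblinding, make the primary analysis censoring-aware with consultation number as the time axis: a discrete-time survival model, or Cox/log-rank. The event is diagnosis confirmed or excluded. Participants undiagnosed at 6 months or withdrawn are censored at their last attended consultation, and their visit count is not imputed as ordinary missing data.

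Report the restricted mean number of visits per arm, with the restriction point fixed in advance, to stay close to the 2.94 versus 2.18 scale. Keep Poisson regression as a sensitivity analysis, with robust standard errors and a stated rule for undiagnosed participants. Report the number undiagnosed by arm and visit spacing by arm, since these determine the size and direction of the bias.

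The cost is wording only: the pro-forma is already completed after every consultation, so no new data are needed. There are two downsides. The main effect becomes a hazard ratio, which the restricted mean only partly offsets because it is not the same quantity as the unrestricted mean. Censoring at withdrawal is also assumed to be non-informative and, because the 6-month limit is in calendar time, visit spacing is assumed unrelated to the number of visits a participant would need. Both assumptions should be examined in a sensitivity analysis.

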#### Secondary outcomes

The secondary outcomes obtained from the pro-forma are:
Number of days and duration of visits (in minutes) until a confirmed diagnosis is reached.Clinical confidence in diagnostic decision. Clinicians will be required to rate the confidence of their decision on a 7-point Likert scale (Definitely ADHD-Definitely not ADHD).Stability in diagnosis. Clinicians will be required to re-rate their diagnostic decision and confidence at 6 months.

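### Stability of the 7-point confidence rating inherits the kappa and logistic approach set for a yes/no diagnosis; read literally, a one-step drift counts the same as a reversal

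*Protocol article*

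**What the plan says.** Under Secondary outcomes, the Protocol article has clinicians "rate the confidence of their decision on a 7-point Likert scale (Definitely ADHD-Definitely not ADHD". The rating is repeated later: "Clinicians will be required to re-rate their diagnostic decision and confidence at 6 months".

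Under Data analysis plan, the diagnosis comes first: "κ Statistics will be used to reflect the stability of diagnosis between first confirmed diagnosis and diagnosis rerated at 6-month follow-up time". Kappa is to be given for each arm, and "the stability of diagnosis will be compared between arms using logistic regression". The next sentence extends this to confidence: "The same analysis approach will be implemented to explore the stability of diagnosis confidence", again between the first confirmed diagnosis and 6 months.

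The text does not mention kappa weights, an ordinal form of the logistic model, or what counts as a stable confidence rating. The level of confidence has its own analysis: "To compare clinician's confidence in their diagnostic decisions, multilevel modelling with patient as a level 2 unit will be used".

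**The concern.** The diagnosis is treated as confirmed or excluded. On two categories, kappa weights have no meaning, and a logistic model of stability is binary: same or changed. Carrying the same approach to the confidence rating therefore points to unweighted kappa and a same/changed outcome.

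On this scale, distance is the content. One step is a small revision of certainty; the full length of the scale is a reversed opinion. Unweighted kappa scores every non-identical pair as full disagreement, and a same/changed outcome does likewise. An arm in which clinicians make small revisions and an arm in which they reverse themselves could look alike, or be ranked the wrong way round.

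**Working it through.** **Figure in the plan.** The document states no kappa, agreement rate or power for stability of confidence, so there is nothing to reproduce. What follows is illustration.

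**Inputs.** From the document: seven ordered categories and two ratings per patient. Assumed: the distribution of the first rating (uniform, or U-shaped with more ratings at the ends), the chance of an unchanged rating (50% to 80%), and the pattern of changes (one step, random, or to the mirror-image category).

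**Formula.** Kappa = 1 − D_obs/D_exp. D_obs is the mean disagreement score over the observed pairs; D_exp is the same mean if the two ratings were independent with the same marginals. The score is 0/1 (unweighted), the absolute distance (linear) or the squared distance (quadratic).

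**Worked case: uniform first rating, 70% chance of no change.**

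*One-step drift.* End categories move to their only neighbour; the others move up or down equally.
- Unweighted: D_obs = 0.30 and D_exp = 1 − 1/7 = 0.857, so kappa = 1 − 0.30/0.857 = 0.65.
- Quadratic: D_obs = 0.30 × 1² = 0.30. D_exp is the sum of the two variances (the means are equal). The first variance is (49 − 1)/12 = 4. The second marginal is (0.85, 1.15, 1, 1, 1, 1.15, 0.85)/7, with variance 2 × (9 × 0.85 + 4 × 1.15 + 1)/7 = 3.786. Kappa = 1 − 0.30/7.786 = 0.96.

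*Mirror-image reversal.* Each non-middle category has a 30% chance of moving to its opposite; the middle is its own mirror image, so overall agreement is (6 × 0.7 + 1)/7 = 0.743.
- Unweighted: kappa = 1 − 0.257/0.857 = 0.70.
- Quadratic: D_obs = 0.3 × 2 × (36 + 16 + 4)/7 = 4.8 and D_exp = 4 + 4 = 8. Kappa = 1 − 4.8/8 = 0.40.

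*Random change.* The 30% is spread equally over the other six categories (0.05 each).
- Unweighted: kappa = 0.65, as for drift.
- Quadratic: D_obs = 0.05 × 7 × 8 = 2.8 and D_exp = 8. Kappa = 1 − 2.8/8 = 0.65.

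| Pattern of change | Unweighted | Linear | Quadratic |
|---|---|---|---|
| One step | 0.65 | 0.87 | 0.96 |
| Random | 0.65 | 0.65 | 0.65 |
| Mirror-image | 0.70 | 0.55 | 0.40 |

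**Same/changed comparison.** If one arm drifted and the other reversed, the odds of an unchanged rating would be 0.70/0.30 = 2.33 and 0.743/0.257 = 2.89. The odds ratio is 2.89/2.33 = 1.24 in favour of the reversing arm. That extreme contrast shows that using one statistic in both arms does not by itself protect the comparison.

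**Range over all assumed tables** (uniform and U-shaped, 50% to 80% unchanged):
- One-step changes: unweighted kappa is lower by about 0.15 to 0.40 than linear and 0.21 to 0.56 than quadratic.
- Random changes: it is lower by 0 to about 0.04.
- Mirror-image changes: it is higher by about 0.10 to 0.25 than linear and 0.18 to 0.50 than quadratic.

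**A smoother model.** Cutting bivariate normal pairs with correlation 0.8 into seven evenly used categories gives unweighted kappa 0.26 and quadratic 0.76; 36% of pairs are identical and 75% lie within one point. Nearby changes dominate in this model, so it shows only the understating direction.

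**The case against.** A reader might infer that the plan fixes unweighted kappa and that stability of confidence will be badly understated. The document supports neither step.

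- It never says plain or unweighted. Weighted kappa is a kappa statistic, and logistic regression includes proportional-odds models. A binary model could also use another cut, such as within one point. A condensed article may leave such details to a fuller plan that is not shown.
- The direction is unknown. No rating distribution or pattern of change is given; the tables show that unweighted kappa can be lower than, equal to or higher than the weighted form. The two forms also measure different things, so a lower value is not in itself a bias.
- A reversal of the diagnosis would not go unseen, because kappa and logistic regression are applied to the diagnosis itself. The multilevel model also covers the confidence ratings.
- The analysis is exploratory.

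Most of this stands, and it limits the point. It does not remove it. The sentence is not mere silence: it assigns to an ordered scale the method just described for a diagnosis, and a weighted kappa or ordinal model would be a different approach from that one. The analysis of the diagnosis cannot grade shifts of certainty that leave the diagnosis unchanged. The multilevel model compares the level of confidence between arms; it does not measure agreement within a patient, since upward and downward revisions can cancel in a mean.

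**Conclusion.** The point holds in conditional form. Taken literally, the planned approach ignores distance on a scale where distance carries the meaning. Stability of confidence would be understated if changes are mostly small, overstated if they are mostly reversals, and little affected if they are spread at random. In the worked case unweighted kappa even puts reversal (0.70) above drift (0.65), while quadratic weighting gives 0.40 and 0.96. These sizes rest on assumed tables and show what can happen, not what this trial will find. The consequence is minor: an exploratory analysis of a secondary outcome, with the primary outcome and the sample size untouched.

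**What to change.** Replace the carried-over sentence with one specific to the confidence ratings:

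- In each arm, report weighted kappa with the weights stated in advance, or the intraclass correlation, with a confidence interval. Linear or quadratic weights are both defensible; what matters is that the choice is fixed beforehand.
- Compare arms by an ordinal or linear model of the 6-month rating adjusted for the rating at first diagnosis, or by a model of the absolute change. The first rating is made after randomisation, so the adjusted model describes revision of opinion rather than a baseline-adjusted effect. Absolute change is the more direct measure of stability.
- Keep ordinary kappa and binary logistic regression for the yes/no diagnosis.

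If a fuller analysis plan already says this, a cross-reference is enough. The cost is wording only: the same two ratings are used and no further data are needed.
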